## Abstract

**Background:**

Treatment of acute myocardial infarction has been the subject of studies over the past years. However, the initial months after myocardial infarction are crucial from the perspective of the patient’s prognosis. It is extremely important to take care of all cardiovascular risk factors and undergo a full rehabilitation program. Telemedical solutions are becoming more and more relevant in everyday practice. We describe a protocol of a study evaluating the use of the mobile application “afterAMI” in patients after myocardial infarction. The app offers an educational mode, calendar, vital signs diary, medication reminders, medical history card, and healthcare professional contact panel. It offers several solutions, which individually proved to be effective and improve a patient’s prognosis. Despite general promising results from previous studies regarding telemedical tools, there is a paucity of evidence when it comes to prospective randomized trials. Our aim was to perform a comprehensive evaluation of a newly developed mobile application in the clinical setting.

**Methods:**

A group of 100 patients with myocardial infarction on admission at the 1st Chair and Department of Cardiology, Medical University of Warsaw, will be recruited into the study. The project aims to assess the impact of the application-supported model of care in comparison with standard rehabilitation. At the end of the study, cardiovascular risk factors will be analyzed, along with rehospitalizations, the patients’ knowledge regarding cardiovascular risk factors, returning to work, and quality of life. In this prospective, open-label, randomized, single-center study, all 100 patients will be observed for 6 months after discharge from the hospital. Endpoints will be assessed during control visits 1 and 6 months after inclusion into the study.

**Discussion:**

This project is an example of a telemedical solution application embracing everyday clinical practices, conforming with multiple international cardiac societies’ guidelines. Cardiac rehabilitation process enhancements are required to improve patients’ prognosis. The evidence regarding the use of the mobile application in the described group of patients is limited and usually covers a small number of participants. The described study aims to discuss whether telemedicine use in this context is beneficial for the patients.

**Trial registration:**

ClinicalTrials.govNCT04793425. Registered on 11 March 2021.

**Supplementary Information:**

The online version contains supplementary material available at 10.1186/s13063-022-06463-x.

## Administrative information

Note: the numbers in curly brackets in this protocol refer to SPIRIT checklist item numbers. The order of the items has been modified to group similar items (see http://www.equator-network.org/reporting-guidelines/spirit-2727-statement-defining-standard-protocol-items-for-clinical-trials/).

## Background and rationale {6a}

Cardiovascular diseases are the leading cause of death and a focal contributor to disability. Managing acute myocardial infarction (AMI) has improved significantly over the past years due to progress in both pharmacotherapy and invasive procedures. The mortality rate following AMI varies between countries, but an overall decrease has been observed [1]. Nevertheless, 12% of the patients die within one year after AMI [2]. Therefore, efforts should be made to optimize the cardiac rehabilitation process. It is crucial to focus on preventing future ischemic events by providing optimal care for patients at-risk [3]. Secondary prevention aims to control all cardiovascular disease (CVD) risk factors, which may be challenging in everyday practice. Jankowski et al. reported that only 2.9% of patients with coronary artery disease (CAD) have all CVD risk factors adequately controlled corresponding to values recommended in the guidelines [4]. Proper CVD risk factor control remains a challenge in the real-world setting.

Several efforts are being made to improve patients’ prognosis. The latest approach to improve cardiac rehabilitation is the use of novel telehealth-based solutions. Over 3.2 billion smartphones are used globally, and the mobile applications market is expected to grow by 18.4% between 2018 and 2026. Therefore, enhancing cardiac rehabilitation by mobile application support may be a promising tool. Telemedicine has proved to be an effective solution in clinical scenarios. Widmer et al. demonstrated that augmentation of usual cardiac rehabilitation with an online and smartphone-based program improved CVD risk factor management and reduced rehospitalizations or emergency department visits by 40% (*p*<0.05) [5]. Naturally, not all cardiac patients are capable of using smartphones. Gallagher et al. reported that 54.6% of cardiac patients eligible for attending cardiac rehabilitation used technology for health purposes. Patients used it to access information on health conditions and medications mainly [6]. Coorey et al. concluded in the meta-analysis that mobile applications have a beneficial influence on CVD risk factors control, but more scientific evidence is required to enhance the implementation of telemedicine into clinical practice [7].

Although several international cardiac societies recommend telemedicine use [8, 9], evidence-based conclusions are required to adjust specific telemedical tools individually to the patient and improve the prognosis. The influence of mobile application support on cardiac rehabilitation in a European setting is yet to be studied.

### Objectives {7}

This study will aim to determine the effect of mobile application-supported cardiac rehabilitation on CVD risk factors control, rehospitalization, emergency department visits, quality of life, and the ability to return to work. We hypothesized that cardiac rehabilitation enhancement with the mobile application would improve the prognosis expressed by CVD risk factors management and the patient’s quality of life.

## Methods

### Study setting {9}, Eligibity criteria {10}, Who will take informed consent? {26a}, Additional consent provisions for collection and use of participant data and biological specimens {26b}, Explanation for the choice of comparators {6b}, Trial design {8}, Provisions for post-trial care {30}

This protocol is a randomized, open-label, superiority, interventional study with two arms. Participants will be randomized to (1) a control group (CG) with standard cardiological care or (2) a mobile application-supported interventional group (IG). The participants will continue with traditional care after the trial is finished.

This single-center study will be carried out at the 1st Department of Cardiology at the Medical University of Warsaw, an academic, public hospital in the capital of Poland. Cardiologists and fellows of cardiology will conduct all study-related procedures. The Department ensures all treatment options for patients with AMI and during their cardiac rehabilitation process. It is regarded as the leading Department of Cardiology in Poland. The anticipated number of eligible participants is 100.

Inclusion criteria:Signing the informed consent to participate in the studyHospitalization due to myocardial infarction, based on the Guidelines on Fourth Universal Definition of Myocardial Infarction [10]Owning a mobile device with Internet access and the Android/iOS operating systemAge ≥18 years oldPositive results of a test verifying the basic skills of using mobile applications (Supplementary material 1)

Exclusion criteria:Life expectancy shorter than 6 months due to non-cardiac illness (Those with malignant tumors, severe mental illness, and/or uncontrolled systemic diseases were excluded from the present study)Negative test results, regarding everyday mobile application useLack of signed informed consentAge <18 years oldPregnancy or breastfeedingLack of a mobile device with Internet access and the Android/iOS operating system

Participant recruitment will occur daily from Monday to Friday. A study team member will approach every patient presenting with AMI, and the inclusion criteria will be assessed. The study design will be thoroughly described to the patient, including all potential benefits, harms, and ethical implications. Each eligible patient will be proposed to enter the study. Patients will be given time to ask questions and all doubts will be clarified before inclusion into the study. If the patient agrees to participate in the research, the informed consent will be signed in 2 copies: one for the participant and one for the research archives. The informed consent will explain how participant data and blood samples will be handled and where they will be sent. This trial does not involve collecting biological specimens for storage. Every participant will receive a note with a summary of the study design.

Every year approximately 400 patients are hospitalized due to acute myocardial infarction. However, a significant part of those patients are unable to use a mobile application and therefore they do not meet one of the main inclusion criteria. Going further, only some of the patients who meet inclusion criteria are willing to take part in a trial. The recruitment began in December 2020. Approximately 7 patients per month are included in the trial. Last patient recruitment is expected in Q1 2022.

## Assignment of interventions: allocation, blinding

### Sequence generation {16a}, Concealment mechanism {16b}, Implementation {16c}, Who will be blinded {17a}, Procedure for unblinding if needed {17b}

This is an open-label study. Randomization will be performed with an online tool by an independent statistician available at (www.randomizer.org). A hundred sets will be generated, each with a number (1 for CG and 2 for IG). All allocations to CG and IG will be executed before the study begins. The list of subsequent allocations will not be visible for the recruiting physician until the initial eligibility assessment of the patient and obtaining the patient’s consent for study participation. After collecting the initial documentation, the physician will be unblinded and will receive the group allocation information from the principal investigator. It should be underlined that the person who checks for inclusion criteria and introduces the patient into the trial protocol is blinded until patient agreement. Figure 1 shows the study design flow chart, describing all the steps of the study (Fig. 1). The investigator performing statistical analysis will be blinded, as well as nurses collecting blood samples on the follow-up visits. Taking into consideration the use of the mobile application in everyday practice, it is impossible to blind physicians performing follow-up visits. It could be regarded as ethically doubtful, because based on the data provided via mobile application, clinical decisions can be made (i.e., blood pressure treatment augmentation).

**Fig. 1 Fig1:**
[figure not shown]
Study flow chart

### Intervention description {11a}, Criteria for discontinuing or modifying allocated interventions {11b}, Strategies to improve adherence to interventions {11c}, Relevant concomitant care permitted or prohibited during the trial {11d}

Patients in the intervention group will be granted access to the mobile application (afterAMI) during the rehabilitation process. Access to the app is what differentiates the groups. afterAMI app offers several features described below. What is more, a dedicated web page will be used by medical professionals to improve everyday clinical work organization and enable better contact with the patients.

Patients in the intervention group will also be given access to educational data about their diseases. Every educational chapter was prepared by a cardiologist experienced in managing patients after MI.

Additionally, every patient will regularly receive messages with notifications about the recommended lifestyle interventions and promoting adherence to the therapy. The notes focus mainly on cardiovascular risk factors and ways of controlling them. We made na effort to emphasize the importance of everyday lifestyle changes in terms of minimizing the risk of potential ischemic events in the future. The role of physical activity and drug adherence was frequently emphasized. All notes were prepared based on recommendations provided by the European Society of Cardiology [11]. An optimal scheme for message quantity and structure has not been described yet in the case of cardiac patients. In a recent meta-analysis, Bashi et al. concluded that the results of mobile application-assisted patient education generally show a positive, promising result. However, due to poor reporting quality and considerable heterogeneity of applied interventions, further studies are required in order to develop a comprehensive, optimal educational scheme [12]. In another paper, a cardiac telerehabilitation program augmented by a short message service (SMS) delivered to patients once a week, resulted in both physical fitness and quality of life improvements [13]. Based on those reports, the authors of this trial decided to send 2 messages weekly. The notifications are also considered as a strategy to improve adherence to the recommendations.

Another essential feature of the application is a panel dedicated to reporting patients’ vital signs (blood pressure, heart rate, weight, saturation, and glycemia), which will be daily analyzed, and if necessary, a short message will be sent to the patient, advising to present to the primary healthcare clinic or emergency department. Patients will be instructed to report their parameters daily, in case of manually entered data. If the patient has a wrist-worn wearable device, compatible with ‘health; application on iOS or Android, then this data will also be presented in the afterAMI app. For instance, in the case of patients with smartwatches allowing for heart rate measurement with photopletyspography or ECG, these parameters (heart rate, blood pressure, body weight, saturation, and physical activity) will automatically be transferred into the app, directly after measurement. Patients with a pressure gauge without a connection to the mobile phone will have to enter the data manually. Naturally, there is room for error associated with adding the value of a particular parameter, but it can also happen during traditional “notebook” notes. A possible clinical scenario is the detection of an alarming rapid increase in bodyweight, which might foreshadow incoming heart failure exacerbation. Another potential use of the application is reporting rapid pulse. Then, new-onset atrial fibrillation might be suspected. In every case requiring medical confirmation, the patient will be referred to the nearest emergency room. However, all patients will be informed, that they should immediately present to the nearest emergency unit or contact the emergency services, in case of recurring angina or any other acute complaints.

Additionally, the application will send notifications with reminders to take drugs. This solution has been previously evaluated in many studies and proved to be a successful tool in increasing adherence to therapy [14].

Moreover, the application includes a module with air pollution parameters measured amidst the localization set up. If they exceed the alarming levels, the patients will be notified, and it will be suggested to minimize outdoor physical activities

Additionally, a medical history card will be created for each patient, based on the discharge documents from the hospital. This solution aims for the patient always to have brief information about undergoing coronary interventions. This knowledge might be crucial for the physicians performing subsequent percutaneous coronary interventions (PCI) in the future and could potentially decrease time-to-balloon.

Finally, the application offers a contact panel to text message and call the cardiologists at the hospital. We believe that this will translate into better work organization, better time management (as fewer consultations are likely to be missed by patients), and increased patient safety. All patients randomized to IG will be thoroughly trained in application features and capabilities before discharge.

On the contrary, patients randomized to the CG will be provided with the best available care, based on current guidelines and standards of care [15]. What is more, all patients will be provided with intense medical care supervision, as every patient included in the study will have two additional cardiological consultations.

Rehabilitation programs are recommended for every patient hospitalized due to MI. It has been underlined, that it improves a patient’s prognosis. However, the final decision on the participation is up to the patient. It should be noted, that the study is carried out during the COVID-19 pandemic. Some patients are refusing to participate in the rehabilitation program in fear of infection. However, owing to the randomization, the number of patients who refused to attend rehabilitation is expected to be similar between the groups. Rehabilitation programs include regular cardiac consultations with an experienced physician, psychological sessions, exercise training, stress management programs, and dietary recommendations. The patient is offered versatile support for one year after MI. Patients who refuse to take part in the rehabilitation program are managed by a general practitioner. Owing to the randomization, patients’ distribution is expected to be similar in both groups.

All data implemented into the application was prepared by experienced cardiologists with considerable experience in both, clinical practice as well as eHealth use.

The market currently offers a wide variety of mobile applications offering simple features to the general population (i.e., blood pressure diaries). However, as far as the authors know, this is one of the very first digital solutions to combine several previously tested features. Moreover, the number of mobile applications dedicated to MI patients is limited. What is more, the first few weeks and months after discharge can be a considerable challenge in everyday activities, therefore it is crucial to recognize the need to support the patient in this period. The described digital tool should be regarded as an opportunity to improve patients’ prognosis, augmenting the traditional approach with standard practice. The only criterion for discontinuing is the participants’ request. What is more, concomitant care is neither permitted nor prohibited in the trial. At the end of the study, the participants will receive a full report with the results of their assessments after the data is analyzed. At the end of the study, the principal investigator will contact the participants to provide them with final educational materials and information regarding secondary cardiovascular prevention.

### Outcomes {12}, Participant timeline {13}, Plans to promote participant retention and complete follow-up {18b}

All 100 patients will be observed for 6 months after discharge. The endpoints will be assessed twice, during two control visits, in 1- and 6-months, after enrollment. Patients will be called to schedule the control visit’s date after discharge. Additionally, patients in the IG will receive a notification in their mobile app reminding them about the upcoming ambulatory visits.

Figure 2 shows the recommended SPIRIT figure with the participant timeline. Primary outcome includes both need for rehospitalization and/or urgent outpatient visit and assessed between baseline and 6-month control visit. There are five secondary outcomes related to cardiovascular risk factors control: blood pressure, body mass, nicotinism, dyslipidemia and need for rehospitalization and/or urgent outpatient visit assessed between baseline and 1-month control visit. Detailed target values regarding risk factors control have been presented in Table 1 based on ESC Chronic Coronary Syndrome guidelines [16]. Each value will be categorized as met or not. Secondary outcomes will also include quality of life and depression severity assessment (MacNew, EQ-5D-5L, and DASS-21 questionnaires), cardiovascular risk factors knowledge (CVD risk factors identification recommended BP values, desired lifestyle intervention identification). and return to work in case of professionally active patients.

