## Statistical methods

### Statistical methods for primary and secondary outcomes {20a}, Methods for additional analyses (e.g. subgroup analyses) {20b}, Methods in analysis to handle protocol non-adherence and any statistical methods to handle missing data {20c}, Interim analyses {21b}

In terms of the endpoints, we will look at the frequency of the events 6 months after the discharge, since we believe that due to randomization the groups will be similar at the beginning. No other (including no interim) analyses will be performed in the present study. Regarding secondary endpoints, the change from baseline will be assessed and the frequency of the events in case of rehospitalizations and/or urgent ambulatory visits after 1 month. The distribution of continuous variables will be estimated using the Shapiro-Wilk test. Continuous variables presented with normal distribution will be presented as mean values and standard deviations (SD). All continuous variables presented non-normal distribution will be demonstrated as median values and interquartile ranges. In the case of variables with a normal and non-normal distribution, the groups will be compared using the Student's t-test and the non-parametric Mann-Whitney U test. The comparison of qualitative variables between the groups will be performed using the Fisher exact test. In order to compare changes in the values of continuous variables over time, the analysis of variance will be performed. To compare the outcome of the patients, the Kaplan-Meier estimators will be utilized. For quantitative variables, the change from baseline will be assessed. Additionally, in order to diminish differences in sex and age related to group size, propensity score matching analysis will be performed as well. We also plan to conduct a subanalysis in the group of patients who attended rehabilitation, as well as in those who did not attend.

A per-protocol analysis will be performed after completing all of the follow-up visits. In the analysis, we will include all patients who meet inclusion criteria and sign informed consent regardless of the follow-up completion. Statistical calculations will be performed twice; after obtaining data from the first follow-up visit from all patients and after the final follow-up, 6 months after discharge. In case of missing data, patients will be excluded from the particular analysis.

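### Only intervention patients are stated to get a reminder of the outcome visits, so attendance and missing data may differ by arm and could bias the comparison

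*Protocol article*

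**What the plan says.** The protocol's section on outcomes, timeline and retention ({12}, {13}, {18b}) ties outcome measurement to two visits: "The endpoints will be assessed twice, during two control visits, in 1- and 6-months, after enrollment". For retention it gives everyone the same first step: "Patients will be called to schedule the control visit’s date after discharge". The next sentence adds a second step for one arm: "Additionally, patients in the IG will receive a notification in their mobile app reminding them about the upcoming ambulatory visits".

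The section on secondary outcome measures places weighing, the smoking question and the repeat cholesterol measurement at those visits. The sample size section ({14}) counts being unable to come to the control visits among the reasons for dropout.

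The statistical methods section ({20a} to {20c}, {21b}) makes three statements about who is analysed. It labels the analysis per-protocol and places it once follow-up has ended. Of the population it then says: "In the analysis, we will include all patients who meet inclusion criteria and sign informed consent regardless of the follow-up completion". Its rule for absent values is: "In case of missing data, patients will be excluded from the particular analysis".

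The intervention description ({11a} to {11d}) says of the panel for texting and calling the cardiologists that "fewer consultations are likely to be missed by patients".

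**The concern.** A retention procedure should not depend on allocation. The two control visits are how this trial obtains its endpoints. A prompt sent to one arm only could make outcome data more complete in that arm, and a patient with no data is left out of the analysis concerned. Randomisation makes the arms comparable as randomised. It does not make those who attend comparable when the arms are prompted differently.

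What is at stake is bias rather than precision. If patients who miss a visit differ in outcome from those who come, unequal attendance removes different amounts of risk from the two arms. A difference can then appear, or a real one be distorted. This applies to the primary endpoint (rehospitalisation or urgent visit) and to LDL cholesterol, weight, smoking and the questionnaires. A larger sample does not cure it.

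**Working it through.** **Route from reminder to analysis.** An app notification goes to one arm, the endpoints are taken at the visits it announces, failure to attend is a dropout reason, and missing data mean exclusion from the analysis concerned. Each link is stated in the protocol. The protocol gives no figure for attendance by arm, so the effect can only be illustrated.

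**The plan's own figure.** With 50% against 20%, power 80% and significance 5% (taken as two-sided), the pooled normal formula is

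n = [1.960·√(2·0.35·0.65) + 0.842·√(0.25 + 0.16)]² / 0.30² = 38.5 per arm.

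This agrees with the stated 38 per group (39 when rounded up; power at 38 is 79.5%). The figure is not in dispute. Recruiting 100 when 76 are required implies an overall loss allowance of 1 − 76/100 = 24%, not split by arm.

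**Illustration 1.** All inputs are assumed: no true effect, event risk 0.40 in both arms, attendance a = 0.95 (intervention) and 0.80 (control), and risk r among non-attenders. The risk seen among attenders is

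(0.40 − (1 − a)·r) / a.

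| r | Intervention | Control | Spurious difference |
|---|---|---|---|
| 0.20 | (0.40 − 0.01)/0.95 = 41.1% | (0.40 − 0.04)/0.80 = 45.0% | −3.9 points (for the app) |
| 0.40 | 40.0% | 40.0% | 0 |
| 0.60 | (0.40 − 0.03)/0.95 = 38.9% | (0.40 − 0.12)/0.80 = 35.0% | +3.9 points (against the app) |
| 0.80 | (0.40 − 0.04)/0.95 = 37.9% | (0.40 − 0.16)/0.80 = 30.0% | +7.9 points (against the app) |

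**Illustration 2, nearer the planning figures.** Equal true risk p in both arms; no-show m = 5% (intervention, assumed) and 24% (control, the whole implied allowance placed there). Patients with an event are k times as likely to miss the visit as those without. The no-show probability is q0 = m/(k·p + 1 − p) without an event and q1 = k·q0 with one. The observed risk is p(1 − q1)/(1 − m).

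- p = 50%, k = 2: control q0 = 0.24/1.5 = 0.16 and q1 = 0.32, giving 0.5·0.68/0.76 = 44.7%; intervention 49.1%; difference +4.4 points.
- p = 50%, k = 0.5: control 55.3%, intervention 50.9%; difference −4.4 points.
- p = 20%: +3.5 points for k = 2 and −2.3 points for k = 0.5.
- p = 50% with control no-show of 35%: 8.1 points in either direction.
- k = 1 (no-show unrelated to events): 0.
- Equal no-show in both arms (5% or 24%): 0 for every k tried.

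**Power.** Taking 50 patients per arm, 5% and 24% loss leave 47.5 and 38 analysed, with power 83.9%. At 10% and 38% loss (45 and 31 analysed) it is 78.8%. Power is little affected, so bias is the issue.

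**The case against.** Five points can be made on the other side.

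1. **No unequal attendance is shown.** A reader might infer that attendance will differ. The documents do not say so. Both arms are telephoned, and the number and timing of those calls are not given; a call close to the visit would act as a reminder in itself. This stands, so the point is limited to what may happen.

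2. **The remark about missed consultations.** A reader might take it as the protocol's own forecast of better attendance at the outcome visits. It follows the description of the contact panel and concerns neither the visit notification nor the two control visits specifically. It is weak support, and the point does not need it.

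3. **The reminder is part of the package.** Access to the app is what distinguishes the arms, and the extra consultations are described as care as well as measurement. Disabling the app's reminder would change what is being tested, and that objection stands. It does not apply to adding an equivalent reminder for controls.

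4. **The analysis includes everyone.** The statistical section includes all consented eligible patients whatever their follow-up, and Kaplan-Meier estimators can use partial follow-up. But the same paragraph excludes patients from any analysis for which they lack data, so the inclusion sentence does not supply a missing outcome. Censoring at last contact is harmless only if non-attendance is unrelated to events, which is the same condition again. The conflict between the per-protocol label and the inclusion sentence is a separate matter.

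5. **The sizes are assumed and modest.** Shifts of 4 to 8 points compare with a planned difference of 30 points (50% against 20%), and the 8-point case in the first illustration needs non-attenders to have twice the average risk. This is fair and limits the weight of the point.

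**Conclusion.** The point holds in a limited form. The protocol states a retention aid for one arm only, for the visits at which endpoints are assessed, and pairs it with exclusion for missing data. Attendance and missingness may therefore differ by arm. Bias follows only if non-attendance is related to outcome, which is plausible when the outcome is rehospitalisation or an urgent visit.

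Size and direction cannot be known from the documents. The first illustration gives about 4 to 8 points, in favour of the app or against it according to whether non-attenders have lower or higher risk than average. It rests wholly on assumed attendance of 95% against 80%, a 40% event risk in both arms, and non-attender risks of 20% to 80%. A reader might infer that the design favours the app; the documents do not support that, since the sign depends on who stays away. The matter should be corrected because the remedy is cheap, but it does not by itself invalidate the trial.

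**What to change.** - Leave the app unchanged. Send control patients an equivalent reminder (SMS or call) at the same interval before each remaining study visit as the app uses.
- For non-attenders in either arm, collect the primary endpoint by telephone with one common script.
- Report attendance at each visit by arm.

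**Cost.** With about 50 control patients and two visits, at most 50 × 2 = 100 messages, plus a few calls. Fewer are needed at this stage. The protocol version is dated 21 February 2022, with recruitment due to end on 31 March 2022. At about 7 inclusions a month, some 7 × 6 = 42 enrolled patients, and those still to be enrolled, have their 6-month visit ahead; about half of them would be controls if allocation is even. Most 1-month visits are already past.

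**Downside.** If the change is introduced mid-trial, earlier visits will have been held under the unequal reminder regime. The date of the change should be recorded and reported. The telephone collection helps regardless of which regime a patient was under.
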